## Abstract

**Background:**

Malaria is a major health issue that is distributed across 85 countries globally including Indonesia. Indonesia is in the process of achieving malaria elimination. Currently, a high burden of malaria exists in the rural eastern part of the nation, including East Nusa Tenggara Province where the number of malaria cases increased significantly during COVID-19. To achieve malaria elimination, malaria awareness must be measurable and integrated into malaria policy. Currently, malaria awareness among rural communities in the region is low, and interventional studies aiming at improving malaria awareness in rural areas in Indonesia are poorly documented.

**Objective:**

This study aims to investigate the impact of a local wisdom-based health education campaign combining local music, the voice of subdistrict leaders, and loudspeaker announcements on malaria-related behaviors in rural communities. Specifically, we aim to assess the effect of this intervention on (1) improvement in the malaria awareness index among rural communities and their associated factors, (2) changes in appropriate malaria treatment-seeking behavior (AMTSB) and its associated factors, (3) enhancements in knowledge and practice of malaria prevention measures and their associated factors, and (4) increased use of long-lasting insecticide-treated nets and their associated factors.

**Methods:**

This study used a cluster-assigned quasi-experimental design with pretest and posttest assessments in control and intervention groups. The control group, consisting of 12 villages, received malaria education integrated into routine health services provided by local health centers. The intervention group, comprising 13 villages, received the same education as the control group, in addition to a malaria campaign conducted once a week for 20 weeks. Before and after the campaign, a household survey was conducted to assess behavioral aspects of malaria, including general knowledge of malaria, AMTSB, and malaria prevention measures knowledge and practice. Improvement in the malaria awareness index, AMTSB, good level of malaria prevention measure knowledge, and good level of malaria prevention measure practice will be determined based on the difference scores for each index before and after the intervention in both groups. The chi-square test will be used to assess score differences. Binary logistic regression analysis will be conducted to identify key risk factors associated with changes in each index.

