#### Phase II (Baseline Phase)

After securing the necessary approvals and obtaining the recommendation letter from the relevant authorities, the research team conducted a household survey with both the intervention and control groups. Before data collection, respondents were provided with a general overview of the study, and informed consent forms were obtained before their participation. The survey aimed to assess behavioral aspects of malaria and was conducted using a questionnaire that had been modified from a previous study conducted in rural ENT Province [67]. The questionnaire consisted of 40 questions designed to collect data on key malaria-related behaviors, including general knowledge of malaria, treatment-seeking behavior, and the use of malaria prevention methods. The questionnaire was completed by either the head of the household or another household member aged 18 years or older.

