#### Phase IV (Evaluation Stage)

At this stage, the research team conducted a household survey in both the intervention and control groups using the same questionnaire that was administered during the baseline phase of the study. The final data collection was done from the third week of January 2025 to the second week of February 2025. Since the research aims to assess the impact of the intervention on all rural adults, participants surveyed before and after the intervention may differ, depending on respondent availability during the data collection period.

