### Outcome Variables

The study considers 10 potential outcomes variables, with the first 7 serving as the primary outcomes of the intervention, while the remaining 3 represent secondary findings. The first primary outcome of the study is improvement in the malaria awareness index among rural communities. If the malaria awareness index after the intervention is higher than that before the intervention, it indicates that the health education campaign effectively enhanced malaria awareness. This index will be assessed based on 12 questions covering general knowledge of malaria, treatment-seeking behavior, and knowledge of malaria prevention measures, following the methodology of a previous study [39]. Each correct response will be assigned a score of 1, while incorrect answers will receive a score of 0, with a total possible score of 12. Participants’ knowledge level will be categorized based on their accuracy rate: 0% (zero awareness), 1% to 59% (poor awareness), 60% to 79% (good awareness), and at least 80% (excellent awareness). Those classified as having excellent or good awareness will be considered aware of malaria, while participants in the other categories will be classified as unaware of malaria [39,70]. The malaria awareness index will be calculated before and after the intervention in both the intervention and control groups to evaluate the effectiveness of the health education campaign.

The second outcome variable in this study is improvement in AMTSB. This improvement will be demonstrated if the proportion of rural adults exhibiting AMTSB after the intervention is higher than before the intervention. AMTSB is defined as seeking malaria treatment at professional health facilities within 24 hours of experiencing malaria symptoms [41]. The proportion of rural adults engaging in AMTSB will be calculated both before and after the intervention in both the intervention and control groups. This assessment will be based on the 3 key questions from the malaria treatment-seeking behavior section of the questionnaire.

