### Statistical Analysis

All statistical analyses will be conducted using SPSS version 27 (IBM Corp), and *P* values <.05 will be considered statistically significant.

For the first outcome variable, descriptive statistics will be used to summarize participants’ sociodemographic characteristics and environmental variables including gender, age group, SES, education level, family size, distance to the nearest health facilities, village accessibility, and household location. A chi-square test will be applied within each study group (intervention and control) to evaluate the association of basic malaria understanding, basic malaria knowledge, the level of malaria knowledge, and the level of malaria awareness before and after the intervention. Unpaired sample *t* tests will be used to investigate the statistical differences. Comparisons will be performed within groups (pre- and postintervention) and between groups to determine the impact of the intervention [61]. Furthermore, a binary logistic regression model will be used to identify the potential factors associated with malaria awareness in both the intervention and control groups [39].

For the second outcome variables, descriptive statistics will be used to summarize participants’ sociodemographic and environmental characteristics including gender, age group, SES, education level, family size, distance to the nearest health facilities, access to village, and household location for both study groups. A chi-square test will be used to evaluate the association between AMTSB and the sociodemographic and environmental characteristics of participants. Unpaired samples *t* tests will be used to assess the statistical differences. Comparisons will be conducted within and between groups for both pre- and postintervention periods. Moreover, binary logistic regression analysis will be used to identify predictors associated with AMTSB among participants in both study groups [41]. Only predictors that demonstrate statistically significant differences (*P*<.05) will be retained in the final model.

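### The abstract promises risk factors for change in each index, but the stated logistic regressions model status and include no interaction with survey wave

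*Protocol article*

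**What the plan says.** The Methods part of the abstract makes two statements about change. Improvement in the awareness index, appropriate malaria treatment-seeking behaviour (AMTSB), good prevention knowledge (MPMK) and good prevention practice (MPMP) "will be determined based on the difference scores for each index before and after the intervention in both groups". Then: "Binary logistic regression analysis will be conducted to identify key risk factors associated with changes in each index".

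The first objective in the abstract concerns "improvement in the malaria awareness index among rural communities and their associated factors". The other three are built the same way, around a change or increase and its associated factors.

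The Statistical Analysis section names the dependent variables. For the first outcome, "a binary logistic regression model will be used to identify the potential factors associated with malaria awareness in both the intervention and control groups". For the second, "binary logistic regression analysis will be used to identify predictors associated with AMTSB among participants in both study groups". The regressions for MPMK and MPMP follow the same pattern, and those for bed nets model use in the dry season or in each season. Under Outcome Variables, awareness is coded as a two-level status: "Those classified as having excellent or good awareness will be considered aware of malaria".

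On who is surveyed, Phase IV says that "participants surveyed before and after the intervention may differ, depending on respondent availability during the data collection period". Phase II adds that "The questionnaire was completed by either the head of the household or another household member aged 18 years or older". The pre/post comparisons of the four indices use unpaired tests, and no linkage of individuals is described.

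**The concern.** A model with awareness or behaviour as its outcome estimates who is aware, or who behaves appropriately. It does not estimate in which groups awareness or behaviour moved. If a factor has the same odds ratio with awareness before and after the campaign, it has no association with change on the odds scale, yet a status model will correctly report it as associated with awareness. Placed under the abstract's label, that result becomes a risk factor for change.

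What is at stake is the associated-factors part of the conclusions. Long-standing differences, for example by education or socioeconomic status, could be presented as factors behind improvement. Conversely, a group that caught up during the campaign could be missed because by the second survey it no longer differs from the rest. The comparison of the two arms before and after the campaign is a separate matter and is not touched by this point.

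**Working it through.** **The plan's own figure.** This point rests on no stated number. The sample size does reproduce: 1.96² × 0.488 × 0.512 / 0.05² = 383.9, taken as 384; 384 × 2 = 768; 768 × 1.15 = 883.2, taken as 884. It is a precision calculation for one prevalence, so it says nothing about power for factors associated with change.

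**Promise against model.**
- Abstract: regression target is change in each index.
- Statistical Analysis, outcomes 1, 2, 3 and 6: regression target is awareness, AMTSB, MPMK and MPMP.
- Statistical Analysis, outcomes 4 and 5: regression target is bed net use in a season.
- Terms crossing a factor with wave, or with arm and wave: none stated.

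**Does status stand in for change?** Take a two-level factor X in one arm. All rates here are assumed, for illustration. Odds are p/(1 − p).

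Example A: X=0 goes from 30% to 40%; X=1 goes from 60% to 70%.
- Pre-wave odds ratio: (0.60/0.40) / (0.30/0.70) = 3.50.
- Post-wave odds ratio: (0.70/0.30) / (0.40/0.60) = 3.50.
- Ratio of post to pre odds ratios: 3.50/3.50 = 1.00.
- Difference in change: (70 − 60) − (40 − 30) = 0 points.

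X is strongly tied to status and unrelated to change on either scale.

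Example B: X=0 goes from 30% to 60%; X=1 stays at 60%.
- Pre-wave odds ratio: 3.50, as above.
- Post-wave odds ratio: (0.60/0.40) / (0.60/0.40) = 1.00.
- Ratio of post to pre odds ratios: 1.00/3.50 = 0.29.
- Difference in change: (60 − 60) − (60 − 30) = −30 points.

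X shows nothing in a post-wave status model, yet change differs by 30 points.

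**Does pooling rescue it?** The article does not say whether waves or arms are pooled. If both waves are pooled with wave as a main effect only, the model forces one odds ratio for X across waves. In Example A it would return 3.50, still a status association. Without a factor-by-wave term the quantity promised is not estimated under any pooling.

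**Which kind of change can be studied?** If respondents are unlinked, the share moving from unaware to aware is bounded only by max(0, p₁ − p₀) and min(1 − p₀, p₁). With p₀ = 48.8% (the prevalence used under Sample Size Calculation) and an assumed p₁ = 58.8%, that is 10.0% to 51.2%. Individual change is thus almost undetermined, whereas the change in the proportion, 10 points, is estimable. Population-level change is the workable target.

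**Cost in precision.** Let V be the variance of a log odds ratio in one arm at one wave. With equal V, independent samples and no clustering, a factor-by-wave term in one arm has variance V + V = 2V, and the arm-by-wave-by-factor term 2V + 2V = 4V. Standard errors are therefore about √2 = 1.4 and √4 = 2 times that of the single-wave status association.

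**The case against.** The best defence is that the Methods are consistent within themselves. They define improvement as a higher proportion or index after the campaign than before, and the regression wording describes status openly. The objectives are ambiguous: associated factors may mean factors associated with awareness or AMTSB rather than with their improvement. On that reading only the one abstract sentence is out of line, and rewording it would be enough. This largely stands, and it is why rewording is offered below as a sufficient remedy. It does not remove the mismatch, because that sentence says changes outright.

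It may also be said that model detail belongs in a fuller plan. That holds for pooling and covariates. It does not hold for the dependent variables, which the article states and which differ from what the abstract promises.

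Three stronger readings are tempting and are not supported:
- That the plan fails because it cannot tell which individuals improved, so that difference scores must go. The documents define improvement at group level, and a difference between group proportions or indices needs no linked respondents.
- That models are certainly fitted separately by arm or on the post-wave survey alone. The text does not say so.
- That one could simulate how often a status model flags a factor and call this the plan's error rate. It would be power to detect a real status association under assumed inputs, and becomes an error only when the result is relabelled as change.

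Finally, some respondents may be the same people in both surveys. The abstract's count of 894 can be read as one cohort, while the Results section ties it to the baseline survey. No linked analysis is described either way.

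**Conclusion.** The concern holds in this limited form: the regressions as stated cannot support the abstract's claim about risk factors for change, because they model status and carry no interaction with wave. The size of any resulting error in this trial cannot be given. The two examples, with assumed rates, show only that the discrepancy can be total in either direction: an odds ratio of 3.5 with no difference in change, or an odds ratio of 1.0 with a 30-point difference. The conclusion does not depend on those rates, or on whether waves or arms are pooled. A reader might infer that all four objectives would be answered with the wrong quantity; their wording is too ambiguous to say so.

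**What to change.** Choose one of two routes for each behavioural outcome.

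1. **Keep the claim about change.** Fit one logistic model on both waves and both arms, allowing for clustering. Take factors associated with change from the factor-by-wave term, and factors modifying the campaign effect from the arm-by-wave-by-factor term. Once the three-way term is included, the factor-by-wave coefficient refers to the reference arm only, so say from which model or arm each is read. Because the waves fall in different seasons, a factor-by-wave result alone should not be credited to the campaign. Label all of this exploratory: power is low, there are 25 villages in 4 subdistricts (2 per arm), and the terms would be added after data collection.
2. **Narrow the claim.** Restate the abstract as factors associated with status at each survey, and label the regression tables likewise.

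Under either route, state that difference scores means the difference in group proportions or indices between waves. The term need not be dropped.

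The cost is small: wording, plus some interaction terms on data already collected, within the final-analysis period that Table 1 runs to December 2026. The main drawback of the first route is wide confidence intervals.

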**Results:**

The intervention was conducted from the last week of August 2024 to the second week of January 2025. A total of 894 respondents participated before and after the intervention. The project is currently in progress, with multiple papers being drafted for publication in peer-reviewed journals.

**Conclusions:**

This study is expected to provide significant findings to comprehensively investigate the change in behavioral aspects of malaria due to a local wisdom-based malaria education campaign. The findings could assist stakeholders in Indonesia with developing malaria health policies that are contextually relevant, thereby supporting global efforts to achieve malaria-free status by 2030.

**International Registered Report Identifier (IRRID):**

DERR1-10.2196/66982

## Introduction

Malaria is a major health problem spreading across 85 countries globally, with an estimated 249 million people with malaria in 2022, of which 2% were from the Southeast Asia (SEA) region [1]. The action plan in this region indicates that the entire SEA region is targeted to achieve malaria elimination by 2030 [2]. Two countries in the region, Maldives and Sri Lanka, obtained a malaria elimination certificate from the World Health Organization (WHO) in 2015 and 2016, respectively, while other countries have a high burden of malaria, with India and Indonesia in particular contributing to 88.1% to the total number of malaria cases in the region [1]. One important indicator for a region to be categorized as having eliminated malaria is the absence of local malaria transmission cases for 3 consecutive years [3].

Following the global commitment, Indonesia has also set a national goal to eliminate malaria by 2030 [4]. Much progress has been obtained toward this commitment. Of the total 514 districts, 75.7% have received malaria elimination certificates since 2023 [5], and malaria is currently concentrated in rural areas [4]. However, there is a huge disparity between the western and eastern parts of the country in this achievement. Most of the districts in the western part have been classified as malaria elimination zones, while a limited number of districts have received malaria elimination certificates in eastern Indonesia, including some in East Nusa Tenggara (ENT) Province [5]. ENT Province has 22 districts and is the third largest contributor to malaria cases at the national level [6]. The number of malaria cases increased during the COVID-19 pandemic, from 12,909 in 2019 to 15,830 in 2022 [7]. Of the total number of districts in this province, 9 districts (41%) have received malaria elimination certificates, while the rest are still categorized as high, medium, or low endemic malaria areas [8]. East Sumba District is one of the high malaria-endemic settings in ENT Province, with the total number of malaria cases reaching 5537 in 2022 [9] and the majority of cases due to *Plasmodium falciparum* [10].

Malaria is a complex health issue influenced by multiple factors including *Plasmodium* types [11-13], sociodemographic factors [14-16], environmental factors [17-19], and behavioral aspects of malaria [20]. The distribution of malaria cases shows the different patterns within and between regions, due to variations in the environment, vectors, and social conditions of the local community [21]. Various studies have been conducted in ENT Province as an effort to reduce the incidence of malaria in this area [22-27]. Studies of the aspects of malaria parasites show that the prevalence of *P. vivax* malaria is greater than *P. falciparum* malaria [22-24], and this presents a major challenge for efforts to achieve malaria elimination considering that *P. vivax* malaria treatment requires high public awareness to complete the treatment for 14 days for the optimal results [28]. Studies on malaria vectors in this region show that the prevalence of mosquito biting in this area peaks at midnight both indoors and outdoors [25,26]. Studies of environmental aspects show that increasing the distance of residence from mosquito larval habitats is followed by a decrease of the risk of malaria in all age groups [27]. However, studies on the behavioral aspects of local communities are very poorly documented in ENT Province, though malaria knowledge significantly contributes to achieving malaria elimination [29,30]. Community behavior and their perspectives are very important in the efforts to achieve malaria elimination in certain areas [31-33].

In the context of Indonesia, several studies of community behavior regarding the knowledge and practice of malaria prevention have been conducted in various provinces [34-36]. The results of these studies indicate that community members have the awareness to practice several malaria prevention methods. However, all these observational studies were conducted in the western part of Indonesia where most of the districts have been categorized as malaria elimination zones [6].

Some studies on community behavior regarding the knowledge and practice of malaria prevention have been conducted in ENT Province [37-43]. A study conducted by the National Health Research Agency in 2018 in eastern Indonesia including ENT Province reported significant variations between provinces in terms of malaria prevention practices in rural communities [37]. Other studies on malaria prevention measures knowledge (MPMK) and malaria prevention measures practice (MPMP) in the region indicated that the Tetun ethnic group used traditional plants to prevent malaria [38], the use of mosquito nets was only common in rural communities of low endemic settings [43], and communities in high endemic areas have a low level of MPMK compared with community groups in low endemic areas [44]. Another study of malaria prevention measures revealed that knowledge on long-lasting insecticide-treated nets (LLINs), which are the most effective prevention measures to prevent malaria [33,45], was only common in the high endemic settings in this province [42]. Regarding malaria treatment-seeking behaviors of the local community, the current literature reveals that the prevalence of appropriate malaria treatment-seeking behavior (AMTSB) among rural communities in the province is very low [41]. Research on malaria awareness in this rural community demonstrated that the level of malaria awareness of rural communities in ENT Province was very low [39] and significant variation in malaria awareness was present among ethnic groups, with the Sumba ethnic group having the lowest level [40]. However, they were all observational studies that only observed the behaviors of rural communities at a certain time. The results of experimental studies on the behavioral aspects related to malaria in rural communities in ENT Province are less documented. This indicates that there have been no efforts by various parties to increase malaria awareness in rural communities in this region. Therefore, innovation is needed to increase malaria awareness among rural-dwelling adults who are an important community group to achieve malaria elimination [46]. Increasing malaria awareness in rural communities allows them to seek the right treatment if they are sick [33,47], reduces the prevalence of malaria [48], and accelerates the elimination of malaria [49].

In the global context, the literature indicates that interventional studies have significantly improved malaria knowledge [50,51], encouraged communities to adopt various malaria prevention measures [51-55], and promoted early malaria treatment-seeking behaviors [56]. In Indonesia, experimental studies using video media have substantially increased malaria knowledge among the elderly in Mimika District, Central Papua Province [57], and Kulon Progo District, Special Region of Yogyakarta [58]. However, these studies were conducted with small sample sizes. A current systematic review on interventional studies for malaria and dengue control indicates that the use of various media in interventions has enhanced disease knowledge among both the general population [59] and school communities [60]. However, there is a lack of studies in the Indonesia context focusing on this approach [59].

The use of loudspeaker media [61], use of local-based songs [62], and local government involvement [63] have been identified as highly effective for increasing health awareness among rural communities [61,62]. However, the impact of these three culturally relevant approaches on malaria-related behavioral changes in rural communities in Indonesia remains unexplored, despite rural populations contributing significantly to the country’s malaria burden [4]. Therefore, these interventional studies will fill these gaps with the following objectives: (1) determine the impact of locally based interventions on improving the malaria awareness index among rural communities and their associated factors including sociodemographic factors and environmental variables, (2) investigate the effectiveness of locally based interventions on improving AMTSB among rural communities and their associated factors, (3) assess the influence of a locally based intervention on enhancing knowledge and practice of malaria prevention measures among rural communities and their associated factors, and (4) estimate the effect of a locally based intervention on increasing the use of LLINs in rural settings and their associated factors.

This study is expected to provide significant findings to comprehensively clarify the change in the behavioral aspects of malaria in the rural ENT Province because of the application of a locally based intervention. Improvement in the malaria awareness index, variation in MPMK and MPMP, and a change in malaria treatment-seeking behaviors among rural communities will be recognized. The findings of this study could assist public health policy makers in Indonesia to design malaria policy to boost malaria elimination progress in the country. The findings might also be beneficial for other countries with similar sociodemographic characteristics to support global actions to achieve a malaria-free area by 2030.

